#### Link worker intervention setting.

The NCL ICS supports a diverse population of 1.5 million people across five London boroughs. This site supports many people within a geographically constrained area increasing the feasibility of us identifying adults with CP and mapping community resources. The effectiveness of the link worker in an area of this size will be extremely informative for other ICSs. Potential community resources and needs have been identified through a literature search, consultation with advisory groups and examining results from a qualitative study where we interviewed 22 adults aged 40 and older living in London about their experiences of ageing and use of community resources [26]. We have also mapped community resources in NCL and online resources that could be well placed to meet these different non-medical needs (e.g., community resources that could support someone experiencing pain). These resources will be shared with the link worker who will continue to update and map additional resources during the intervention.

#### Link worker intervention.

The intervention will involve a specialised link worker role based in NCL for a period of 12 months. This link worker will receive bespoke training on living and ageing with CP plus any additional training needs identified by themselves and UP (e.g., motivational interviewing). Following this they will work in the NCL ICS. The link worker will work with adults with CP to determine their individual non-medical needs and then link them into community resources that could support them to improve their health and wellbeing. The process of the link worker intervention is provided in Fig 1.

**Fig 1 pone.0343206.g001:**
[figure not shown]
Flowchart of the link worker intervention, including recruitment, data collection, and intervention phases.

Once informed consent is provided to the postdoctoral researcher (ER), the link worker will contact the eligible participant to arrange the introductory phone call and will send them either the link or the paper version of the baseline questionnaire, which must be completed before the intake meeting. During the introductory phone call the link worker will answer any questions the participant may have in relation to their role and will check whether the baseline questionnaire has been completed. If the survey has not been completed, the link worker will provide assistance before moving forward. If the participant has questions about the study itself, the researcher will be available to answer these and, if needed, arrange a separate meeting with the participant.

After the introductory phone call, the link worker will schedule the intake meeting. This can take place in person, over the phone, or via computer (video call), depending on the participant’s preference. During the intake meeting, the link worker will work with the participant to identify their non-medical needs and main priority areas, and to establish an agreed set of priority goals to be achieved within the intervention. Goals will be tailored to each participant’s needs and should follow the SMART principle – Specific, Measurable, Attainable, Realistic and Timely – with the overall aim of supporting the participant’s wellbeing. To help focus the discussion and ensure areas of needs are prioritised, participants will be asked to identify their top two concerns using a structured tool, based on Goal Attainment Scaling [27] and adapted from existing practice. This tool provides a guide to support the identification and prioritisation of needs, while also allowing flexibility to address other areas the participant wishes to raise. The process of identifying and prioritizing non-medical needs and goals will remain participant led. The intake meeting will last approximately 1 hour.

Based on the intake meeting, the participant’s identified non-medical needs, and the agreed goals, the link worker will develop a social prescription plan detailing recommended community-based activities and services tailored to the participant’s needs. The social prescription will be shared with the participant electronically or in print, based on their preference. The nature and type of community-based resources recommended by the link worker may vary depending on availability at the time of the intervention. The link worker will follow up with the participant after the intake meeting to check on their progress and access to the referred services, to offer additional support if needed, and to help connect them to the community-based services. Due to the person-centred nature of the link worker services, it is difficult to define a standardised duration for the intervention and follow-up(s), as the length and intensity of support are shaped by each participant’s needs and the complexity of their circumstances [28]. As a result, the timing and number of follow-up contacts will be flexible and tailored to each participant’s needs and level of complexity. Some participants may require brief, short-term contacts, while others may need ongoing or intermittent support. The schedule and format of such follow-up contacts will be agreed between the participant and the link worker.

Link worker support will be available for up to three months, although it may finish earlier if the participant and the link worker agree that the intervention has been completed. At the end of the intervention, the link worker will schedule a meeting with the participant to review the progress made and the extent to which their goals have been achieved. This can take place in person, over the phone, or via computer (video call), depending on the participant’s preference.

If a participant presents with several unrelated non-medical needs, it may be necessary to conduct more than one intake meeting, each resulting in a separate cycle of goal setting and corresponding social prescription. The determination of whether needs are sufficiently unrelated to warrant separate intervention cycles will be made at the discretion of the link worker, based on their professional judgement. To ensure that each cycle can be evaluated separately, each intake meeting (and corresponding social prescription) should occur at least three months after the previous one.

If a participant presents with clinical needs outside the scope of social prescribing, the link worker will escalate the case to the designated supervisor or appropriate staff at UP, who oversee the social prescribing service.

Participants will be encouraged to bring along a supporter or carer should this help them feel more comfortable during any part of the intervention.

#### Link worker role and responsibilities.

In addition to supporting participants, the link worker will be responsible for aspects of data collection, including recording meeting notes (field notes) and assisting with questionnaire administration. The questionnaires and field notes are described in more detail below.

The link worker will also be responsible for maintaining and updating a database of community-based activities and services in NCL, and for connecting with these services. The database includes two components: (1) the list of community resources described above and (2) a selection of directories relevant to social prescribing practice. Throughout the one-year intervention, the link worker will update and add new resources in response to participants’ emerging needs as well as changes in service provision within NCL and will build relationships with local service providers to ensure referral options are relevant and accessible to participants.

Finally, the link worker will contribute to recruitment activities. As part of their role, the link worker will identify and engage with local healthcare and community services within NCL to promote the link worker programme and provide information about the referral process. Moreover, they will help identify and invite community-based service providers and participants’ carers/ supporters to take part in interviews as part of the intervention evaluation at the end of the intervention. The interviews are described in more detail below.

#### Outcome measures.

This study will use a mixed-methods approach, combining quantitative and qualitative data collected through different sources.

Based on previous process evaluations of social prescribing interventions [29,30] and education programmes [31], the process evaluation of the CP link worker intervention will examine reach, dose, fidelity, acceptability, sustainability, and unintended consequences as defined below.

Reach is defined as the extent to which the intended population engages with the intervention. It will be assessed using quantitative data on uptake (e.g., agreement to be referred to the link worker) and engagement (e.g., continued participation in link worker appointments and use of referred community services). Participants’ characteristics will also be analysed to explore potential patterns in engagement and disengagement. To support this, the following data will be collected:

Number of participants invited by the participant identification centres (NHS trusts) to join the link worker programme and who self-referredNumber of participants meeting eligibility criteriaNumber of participants enrolled in the programmeReferral records (date, referral source, reasons for referral)Sociodemographic and clinical characteristics of participantsUse of health and social care servicesRetention rates.

Dose is defined as the number, format (in person, on-line, phone), type (introductory, intake, follow up), and duration of meetings between the participant and the link worker. It will be recorded and assessed using qualitative and quantitative data on the link worker activity collected through the link worker field notes.

Fidelity is defined as the extent to which the intervention is delivered as intended. It will be assessed using both quantitative and qualitative data on the link worker activity, primarily collected through link worker field notes. This will include whether the introductory phone call and the intake meeting were completed, whether participant non-medical needs were identified and goals were set, the number and types of community resources recommended, whether and when the community resources were accessed by participants including reasons for non-access, the number and modality of follow-up contacts made, and whether participants’ goal achievement was reviewed. Participant access to community resources, including timing, waiting periods, and frequency of use, will be triangulated with data from the 3-months follow-up questionnaire to strengthen the assessment of fidelity.

Acceptability is defined as the extent to which the intervention is perceived as appropriate and satisfactory by participants and stakeholders, based on their experiences of its content, delivery, and perceived value. It will be assessed through a 3-month follow-up questionnaire with participants, and they will also be invited to take part in a voluntary interview. In addition, participant dropout and non-engagement rates will be recorded, along with reasons for withdrawal or disengagement, when possible. Semi-structured interviews will be conducted with the link worker, community-based service providers, participant’s carer/ supporter, and the founders of UP to explore perceived acceptability of the intervention.

Potential sustainability is defined as the extent to which the CP link worker intervention can be maintained or embedded within routine practice over time. It will be assessed through interviews with the link worker, community-based service providers, and the founders of UP, exploring perceptions of feasibility for long-term implementation, resource requirements, organisational capacity, and alignment with existing systems.

Unintended events or consequences of the CP link worker intervention will be recorded and explored through the link worker field notes and through the interviews with participants, their carers/ supporters, link worker, community-based service providers, and the founders of UP.

#### Data collection.

The number of people invited to take part in the intervention, those who self-refer, the number of participants enrolled in the programme, and retention rates will be recorded by the researcher throughout the intervention period.

Data will be collected from participants through survey at three time points – baseline, 1-week, and 3-month follow-up – and through a voluntary-based interview at the end of the intervention. Participants will be able to complete the survey either online or on paper. Participants will be asked to complete the survey within one week of receiving it. Participants who require additional support may choose to complete the survey with assistance from their carer/ supporter, the link worker, or request a paper version of the questionnaire by post. The questions asked at baseline, 1-week and 3-months are outlined in Table 1.

**Table 1 pone.0343206.t001:** Data collected from intervention participants.

Domain	Measure	Baseline questionnaire	Intake meeting	1-week follow up questionnaire	3-month follow up questionnaire
Sociodemographic and clinical information	Study-specific items	✓	–	–	–
Use of health and social care services	Use of health and social care services (Understanding Society survey)	✓	–	–	✓
Achievement of participant goals	Goal Attainment Scaling – light model (GAS- Light) [27]	–	✓	–	✓
Psychological wellbeing	World Health Organization-Five Well-Being Index (WHO-5) [32]	✓	–	–	✓
Health related quality of life	EuroQol 5-Dimension 5-Level (EQ-5D-5L) [33]	✓	–	–	✓
Loneliness	UCLA-3 item Loneliness Scale (UCLA-3item) and a direct question about how often the respondent feels lonely [34]	✓	–	✓	✓
Fatigue	One-Item Fatigue Screen (OIFS) [35]	✓	–	✓	✓
Pain	Single item from EQ-5D-5L [33]	✓	–	–	✓
Social network	Lubben social network scale [36]	✓	–	–	✓
Social group membership and sense of local community	Selected items adapted from [37]	✓	–	✓	✓
Empowerment	Adapted version of the Diabetes Empowerment Scale – Short Form (DES-SF) [38] Individual community-related empowerment scale: Dimension 2 (intention) and 3 (participation) [39]	✓	–	✓	✓
Feedback on the experience with the link worker	NHS Patient Social Prescribing Link Worker Feedback [40]	–	–	✓	✓ (*)
Feedback on social prescription	Study-specific items	–	–	–	✓ (*)
Feedback on the overall intervention	Study-specific items	–	–	–	✓ (*)

Footnote for Table 1: (*) Component also explored in the optional interview at the end of the intervention. Different questionnaires are administered at 1-week and 3-months due to the fact that the 1-week follow-up collects data on outcomes related to the link worker and those measures that require the participant to think about the outcome for a week or less (those questionnaires that require the participant to think about the outcome for more than a week are asked about at 3-months only). The need for different questionnaires at 1-week and 3-months is also due to the fact that at 1-week the participant will be reflecting primarily on contact with the link worker and that at 3-months the participant will be reflecting on contact with the link worker and social prescription (as PPI feedback has indicated that it can take a few weeks for participants to access their social prescriptions).

Throughout the intervention period the link worker will complete field notes – brief written records made during or after interactions with participants or while delivering the intervention. These notes will capture the date, modality, timing, and duration of each interaction, as well as observations, reflections, challenges, and contextual details relevant to the delivery of the intervention. Field notes will be reviewed periodically by the research team to ensure the quality of data collection and to assess adherence to the delivery model, and any adaptations or deviations will be documented along with the rationale for these changes. In addition to the field notes, the link worker will complete an intake form and a social prescription plan for each participant.

After completing the 3-month follow up questionnaire, all participants will be invited to take part in an interview with the research team to discuss their expectations of the intervention, their experiences with the link worker, and the activities to which they were referred. The interview will also explore their views on what worked well and what could be improved. Participation is voluntary, and refusal will not affect involvement in the study. The interview will be conducted either online, over the phone, or in-person depending on the preference of the interviewee and will last around 60 minutes. To help reduce potential anxiety, the list of interview questions will be shared with interviewees one day before the interview. The accompanying message will clarify that no preparation is required for the interview unless the interviewee chooses to do so. Interviewees will also be able to contact the research team up to one week after the interview to share any additional thoughts or reflections.

Withdrawal from the intervention will be defined as either an explicit decision communicated by the participant (or their carer/ supporter) to the research team to discontinue their involvement (active withdrawal) or non-engagement despite repeated follow-up attempts (passive withdrawal). Passive withdrawal will be defined as non-engagement after three unsuccessful follow-up attempts by the link worker within one month, using a combination of methods (phone, email, and post). No further contact will be made by the link worker after this point. Withdrawal may occur at one of three stages: prior to the introductory phone call with the link worker, after receiving the social prescription, or during the 3-months follow-up period for data collection. In the event of participant withdrawal, the research team will invite participants to complete a brief withdrawal questionnaire online or on paper to capture the reason for disengagement and gather feedback on the intervention. In case of non-engagement, the reason for withdrawal will be recorded as unknown.

At the end of the intervention, semi-structured interviews will be conducted with the link worker, community-based service providers, participants’ carers/ supporter, and the founders of UP involved in the training and supervision of the link worker. Interviews will be conducted online, over the phone, or in-person depending on the preference of the interviewee. The same interview procedures used with intervention participants will be used with stakeholders, including advance sharing of interview questions and a one-week window for post-interview reflections.

The development of the questionnaires and the interview topic guides has been informed by previous evaluation studies of social prescribing interventions [29,37,41,42], as well as by discussions with the study’s advisory groups. All questionnaires have been piloted with members of the lived experience advisory group,

Copies of the questionnaires and of the interview topic guides are included on the Open Science Framework [43].

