### Data management

The team will adhere to the principles of the GDPR and University of Surrey policies that are aligned to comply with the Data Protection Act 2018. All data covered by the GDPR will be password protected and kept in a secure University file space. Only the link worker ([name]), staff overseeing the link worker intervention (EL, MC), principal investigator (KS) and post-doctoral researcher (ER) will have access to any non-anonymized data.

All participants will be given a unique pseudonym and participant ID which will be used to identify them on any study documentation. If any participant provides personally identifiable data (e.g., names) for other people/ key places in interviews, this information will be changed in all transcripts. We will also not use any quotes from participants which could make them identifiable. Any identifiable information will be stored separately to anonymized data and records of informed consent.

As per the requirement of our funder we aim to share anonymized data from those participants who consent to this at the end of the project. Prior to this any information that could render a person identifiable will be redacted by the project team. Where participants have not consented to wider sharing, we will remove their data prior to curating and archiving that specific form of data.

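### The link worker may help participants complete the items that rate the link worker, so questionnaire-based acceptability is at risk of upward bias among those assisted.

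*Protocol article*

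**What the plan says.** Help with questionnaires is part of the link worker's job. Under Link worker role and responsibilities, "the link worker will be responsible for aspects of data collection, including recording meeting notes (field notes) and assisting with questionnaire administration". Under Data collection, participants who need support "may choose to complete the survey with assistance from their carer/ supporter, the link worker, or request a paper version". For the baseline form, the text after Fig 1 adds: "If the survey has not been completed, the link worker will provide assistance before moving forward".

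Table 1 lists three feedback components. The "NHS Patient Social Prescribing Link Worker Feedback" form is given at 1 week and 3 months. Study-specific feedback on the social prescription and on the overall intervention is given at 3 months. None of the three is given at baseline.

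Of acceptability, Outcome measures says: "It will be assessed through a 3-month follow-up questionnaire with participants, and they will also be invited to take part in a voluntary interview". It adds drop-out and non-engagement rates with reasons, and interviews with the link worker, service providers, carers/supporters and the founders of the partner charity.

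Data management names the link worker, the staff overseeing the intervention, the principal investigator and the postdoctoral researcher as the only people who "will have access to any non-anonymized data". On the stakeholder interviews, the link worker's duties include that "they will help identify and invite community-based service providers"; the same sentence covers participants' carers/supporters.

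**The concern.** There is one link worker, so the feedback form rates one identifiable person. A participant who cannot read, write or type unaided and has no carer is left, under Data collection, with one named helper: that person. At 1 week the participant may still depend on the link worker, whose support can run for up to three months. People tend to answer more kindly in front of the person they are judging.

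Acceptability is in the overarching aim and in objective 1. A distortion from the way answers are collected does not shrink as more participants are recruited. If nobody records who helped, it cannot be examined afterwards. Need for help probably goes with greater impairment, so the most affected participants could give the least independent ratings.

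A smaller, separate issue is selection. If the link worker helps find the providers and carers to be interviewed, contacts that went well may be over-represented.

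**Working it through.** The plan states no figure on this point, so there is none to reproduce. The check is mainly one of text.

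**1. Is link worker help confined to baseline?** No. The baseline procedure is described separately after Fig 1. The duty of "assisting with questionnaire administration" and the option under Data collection are both general, and the latter directly follows the statement that surveys are given at three time points.

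**2. Are the feedback items excluded from that help?** No exclusion appears in the text, in Table 1 or in its footnote.

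**3. Do the assisted items feed acceptability?** Yes, through the 3-month questionnaire.

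**4. Is the link worker kept from identifiable feedback?** Data management grants access in general terms and makes no exception for feedback. It does not mention the survey by name, so access is not excluded, rather than stated.

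**5. Who selects interviewees?** All participants are invited after the 3-month questionnaire, and the research team interviews them. The link worker's part concerns providers and carers/supporters only, and consists of helping to identify and invite them.

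**6. Scale, on assumptions only.** The document gives neither the share assisted nor any inflation.

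- Shift in the overall percentage satisfied = share assisted × inflation among the assisted.
- Low: 0.25 × 10 = 2.5 points. Middle: 0.50 × 20 = 10 points. High: 0.75 × 30 = 22.5 points.
- With an assumed true satisfaction of 70%, 30 points is the largest inflation possible (100 − 70).

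For comparison, the standard error is √(p(1 − p)/n). The plan recruits 31 and allows 30% drop-out, leaving 31 × 0.70 = 21.7 completers; its power calculation uses 20. With p = 0.70:

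- n = 20: √(0.21/20) = 10.2 points
- n = 22: √(0.21/22) = 9.8 points

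So the shift could be well below sampling error or about twice it.

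**7. Does baseline help cancel the effect?** For scales also measured at baseline (loneliness, empowerment, wellbeing), help at both times could cancel part of any effect on change. The feedback items have no baseline value, so nothing cancels for them.

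**The case against.** Link worker help is optional and meant for those who need it. A carer/supporter or a postal copy is offered as well, and Enhancing accessibility adds phone and in-person collection. Acceptability does not rest on assisted ratings alone. The research team interviews participants about the link worker and about what could be improved. All three feedback components are also explored in that interview. The research team sends a withdrawal questionnaire, and drop-out is counted with reasons. The link worker needs names and contact details to deliver the service, so general access is not in itself improper, and a condensed article may leave the return route of forms to the full protocol. The study also says that it cannot formally determine effectiveness.

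Much of this stands, and it rules out several stronger readings that a reader might infer:

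- **That acceptability is shown to be biased.** The document shows a route to bias and a plausible direction, not that bias occurs.
- **That the link worker chooses the interviewees.** This is untrue for participants, and for providers and carers the role is to help.
- **That the link worker will see the feedback.** No section says so.
- **That the outcome scales must move favourably.** Baseline help may cancel part of any effect.
- **That no acceptability claim could be supported.** The other sources carry real weight.

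The objection does not remove the point. The interview is voluntary and follows the 3-month questionnaire. Withdrawal feedback concerns only those who leave, and for non-engagement the reason is recorded as unknown. A postal copy does not help someone who cannot complete a form alone. Enhancing accessibility lists modes of collection and does not say who assists.

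**Conclusion.** The concern holds in a limited form. Followed as written, the plan lets the one person being rated help complete the rating, and nothing keeps identifiable feedback from that person. Questionnaire-based acceptability is therefore at risk of upward bias among assisted participants. The other acceptability sources offset this in part. Selection of provider and carer interviewees is a smaller risk of the same kind.

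The size is unknown. The range of 2.5 to 22.5 points rests wholly on the assumed share assisted and assumed inflation; it shows only that the effect need not be negligible beside a standard error of about 10 points. The text findings do not depend on those assumptions. The change is cheap and the missing information cannot be recovered later, so it is worth making before follow-up questionnaires accrue.

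**What to change.** In Link worker role and responsibilities and in Data collection, state that:

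- help with the feedback items at 1 week and 3 months comes from the existing postdoctoral researcher or a carer/supporter, not the link worker;
- these responses go to the research team only and are withheld in identifiable form from the link worker and from staff overseeing the role, with Data management amended to match;
- helper and mode of completion are recorded at every time point, and feedback and outcome results are also shown by helper, descriptively given the sample size.

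The change should stay confined to the feedback items. Barring link worker help for every follow-up item while keeping it at baseline would change the helper between time points for loneliness, empowerment and wellbeing. For those scales, keep the type of helper the same as at baseline where possible.

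For stakeholder interviews, the researcher should select providers and carers from the full referral list in the prescription plans, including referrals that were not taken up.

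**Cost.** Some hours of existing researcher time. If 25% to 75% of 31 participants need help, that is about 8 to 23 people per time point before drop-out (0.25 × 31 = 7.75; 0.75 × 31 = 23.25), fewer where a carer assists, and for the feedback items only. Participants who know the link worker lose a little convenience, and there is a small risk of missing feedback items among those who need help.
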